### Secondary Outcomes

#### Wisconsin Stone Quality of Life Questionnaire

Penniston et al [34] developed the WISQOL as a disease-specific measure to assess the QoL of patients with UC. It encompasses 7 dimensions: vitality and fatigue, sleep, work and family, nutrition (diet) and pharmacotherapy, physical conditions, concerns over intimacy and traveling, and emotional status in general [34]. The scale consists of 28 items, each rated on a 5-point scale from 1=very true to 5=not at all true, yielding a total score range between 28 and 140. A higher score indicates a better QoL. This scale is widely used in multicenter studies in various countries, such as the United States and Canada, for its well-confirmed reliability and validity. Cronbach α coefficient was 0.948, and the reliability was 0.907 in the Chinese version.

#### Patient Health Questionnaire-9

This assesses participants’ mental health status after receiving different interventions, which can help monitor the health status and psychological well-being of patients [35]. Nine items with a cumulative score on the Patient Health Questionnaire-9 (PHQ-9) range from 0 to 27. Cronbach α coefficient was 0.839, and the reliability was 0.846 in the Chinese version.

#### International Physical Activity Questionnaire—Short Form

This assesses the participants’ physical activity levels and the frequency and duration of the workout [36], which can affect the fluid requirements and the risk of UC formation. The questionnaire consists of 7 questions to assess physical activity level over the past week. Activity is classified as low if the total score is <600 metabolic equivalent of task-minutes per week and classified as high if it is >3000 metabolic equivalent of task-minutes per week. The intraclass correlation coefficients for all physical activity categories within the International Physical Activity Questionnaire were above 0.7 in the Chinese version.

#### Electronic Health Literacy Scale

This scale is designed by Norman and Skinner [37] to measure an individual’s self-perceived skills in using information technology for seeking, searching, understanding, and appraising health information from electronic sources. Including 8 items with a 5-point Likert scale, the total score ranges from 8 to 40. The Cronbach α coefficient of the eHEALS scale is 0.963. The retest reliability coefficient *r* was 0.984 (*P*<.001) in the Chinese version.

#### The Number of Readmissions, Outpatient Visits, and Emergency Department Visits

This assesses the frequency of hospital readmissions related to UC, including the timing of such readmissions due to stone recurrence or related symptoms (eg, hematuria, pain, and infection) and the number of outpatient visits in terms of UC management. The frequency of emergency department visits is due to UC. Any medications might affect fluid intake or urinary output or improve the symptoms that triggered postoperatively.

#### Recurrence Rate

The rate at which new UC forms during the 3-month follow-up.

#### Frequency of Hematuria or Dark Urine

The frequency of the presence of blood in urine or dark urine, which can be a symptom of a new urinary stone or a signal of less fluid intake.

### Sample Size

An adequate sample size and statistical power ensure that the findings can be reliably generalized to a broader population. The required sample size for hypothesis testing is determined based on the expected effect size [38]. In this study, the sample size will be determined by a statistical tool, G*Power software (Heinrich Heine University Düsseldorf) [39], with an α of .05, a power of 0.80, and an allocation ratio of 1:1. The sample size for this study was calculated based on a comparable RCT that used an eHealth device (an intelligent water bottle) to promote increased fluid intake [18], of which the calculated Cohen *d* was 0.61, and the effect size is considered significant since Cohen *d* is over 0.5. Based on the calculations, a sample size of 92 participants is estimated. Accounting for an attrition rate of 38%, as observed in this research, a total of 148 participants are anticipated to be recruited.

### Randomization, Blinding, and Concealed Allocation

An RCT will be conducted to recruit participants in a single site, the Shekou Free Trade Zone Hospital. Randomization may lead to baseline characteristic imbalances between intervention groups [40]. In small-scale trials, stratification might be beneficial, as it can prevent significant imbalances in factors predicting outcomes [41]. Stratified randomization will be applied to the eligible participants to ensure an equal chance to be allocated to the research field [42]. Balanced randomization aims to create unbiased groups for comparison and also seeks to maintain groups of roughly equivalent size throughout the trial [43]. In this research, convenience sampling will be applied, with block randomization applied using a block size of 10. For every group of 10 participants enrolled in sequence, 5 will be allocated to the intervention group and the remaining 5 to the control group, which will be done by the statistician and urologists who are not engaged in conducting the research interventions.

### Data Collection

The study will be conducted on postoperative patients with UC. It will span 3 periods: T0 (before the intervention), T1 (at the end of 1 month), and T2 (at the end of 3 months). The data collected at each time point will allow for evaluating the intervention’s effectiveness and identifying areas for improvement. Reminders will be sent prior to each follow-up visit using the participant’s preferred method of communication, with a thank-you message after the visit. For any participant who discontinues the intervention prematurely, we will record the reason for their discontinuation and collect any serious adverse events that occurred up to the point of discontinuation.

### Methods of Analysis

The study outcomes will be reported to adhere to the guidelines outlined in the CONSORT (Consolidated Standards of Reporting Trials) 2010 statements [44]. Statistical tests such as a 2-tailed *t* test and chi-square test will be used for continuous and categorical variables within 2 groups. The principal analysis will compare the fluid intake volume between the intervention and control groups using the 2-tailed *t* test. Secondary outcomes such as WISQOL, PHQ-9, and eHEALS will use repeated measures of ANOVA since they are measured over time and between 2 groups. If necessary, subgroup analyses will be conducted to explore whether the effect of the intervention varies across different demographic or clinical subgroups. Intention-to-treat analysis will be used to assess the impact of the treatment and its generalizability as well as the missing data. A planned interim analysis will be performed to evaluate both efficacy (whether the intervention shows sufficient benefit to potentially stop the trial early) and futility (whether the intervention is unlikely to demonstrate benefit if the trial continues) after 50% (74/148) of the target sample size have completed the primary end-point assessment. A significance level of *P*<.05 will be used to determine statistical significance, and all data analysis procedures will be conducted using the SPSS (version 26.0; IBM Corp) software package.

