**Inclusion criteria**
With a history of urinary calculi and having received urolithiasis surgery before.24-hour fluid intake <2500 mL.Age ≥18 years.Able to use WeChat daily.Able to read and write informed consent.

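### The principal t test of fluid intake leaves out the baseline intake already collected: valid and adequately powered, but it gives up precision, as does the likely form of the repeated-measures ANOVA

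*Protocol article*

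**What the plan says.** The Methods of Analysis section names the principal test: "The principal analysis will compare the fluid intake volume between the intervention and control groups using the 2-tailed" t test. It gives no covariate and no time point. WISQOL, PHQ-9 and eHEALS "will use repeated measures of ANOVA since they are measured over time and between 2 groups". The article does not mention baseline adjustment for any outcome.

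Baseline values exist. The Data Collection section describes the study schedule: "It will span 3 periods: T0 (before the intervention), T1 (at the end of 1 month), and T2 (at the end of 3 months". The abstract says that outcomes are measured at all three times. Low intake is also a condition of entry: "24-hour fluid intake <2500 mL". The Results section reports T0 collection as complete.

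The Sample Size section works "with an α of .05, a power of 0.80, and an allocation ratio of 1:1" and Cohen d = 0.61. From these, "a sample size of 92 participants is estimated", raised to 148 for 38% attrition.

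**The concern.** A participant's intake before treatment usually predicts part of their intake afterwards. Using it as a covariate removes that part from the error variance and corrects for chance baseline differences between arms. The article's own randomization section notes that such imbalance can occur and matters more in small trials. A plain t test uses none of this information.

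For the three scales the problem has another form. If T0 enters the ANOVA as an outcome level, the group main effect is averaged over a time when treatment cannot yet have acted, and the group-by-time test spends two degrees of freedom. The stake is wider confidence intervals and lower power than the collected data allow.

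**Working it through.** **Inputs.** From the Sample Size section: two-sided alpha 0.05, power 0.80, ratio 1:1, d = 0.61, 92 completers (46 per arm), 38% attrition. The correlation r between baseline and follow-up is not in the article. It is an assumption, shown as a range.

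**The plan's own figure.** A two-sided t test (noncentral t) at d = 0.61 and 80% power needs 44 per arm, 88 in all. The stated 92 is what the Wilcoxon-Mann-Whitney option gives (efficiency 3/pi, 46 per arm). For the t test, 92 therefore errs on the safe side. Attrition: 92 / 0.62 = 148.4, in line with 148. With 46 per arm the noncentrality is 0.61 × √(46/2) = 2.93 on 90 df, and power is 82.5%.

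**Fluid intake, ANCOVA on T0.** The residual variance is multiplied by 1 − r², so the effective standardised effect is 0.61 / √(1 − r²), on 89 df.

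| Assumed r | 1 − r² | Power, 46 per arm |
|---|---|---|
| t test, no covariate | 1 | 82.5% |
| 0.1 | 0.99 | 82.9% |
| 0.2 | 0.96 | 84.0% |
| 0.3 | 0.91 | 85.8% |
| 0.5 | 0.75 | 91.6% |
| 0.6 | 0.64 | 95.1% |

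**Effect of the entry cap on r.** Suppose intake before selection is normal with mean/SD of 1800/500, 2000/600 or 2300/700 mL (illustrative assumptions), cut off at 2500 mL. Let u² be the ratio of the variance after the cut to the variance before it: 0.745, 0.581 and 0.430. A correlation r becomes r·u / √(1 − r² + r²u²), so 0.5 falls to 0.45, 0.40 and 0.35.

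**Secondary scales.** Assume compound symmetry with correlation r, no effect at T0 and an equal effect d at T1 and T2. The variance per unit of squared effect, in units of the outcome variance, is:

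- Group main effect over T0, T1, T2: the effect is (2/3)d and the variance (1 + 2r)/3, which gives 0.75(1 + 2r).
- ANCOVA of the mean of T1 and T2 on T0: (1 + r)/2 − r².
- ANCOVA of T2 on T0: 1 − r².

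The ratios of these are ratios of required sample size.

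| r | Main effect | Adjusted mean T1/T2 | Adjusted T2 | Main ÷ mean T1/T2 | Main ÷ T2 |
|---|---|---|---|---|---|
| 0.1 | 0.90 | 0.54 | 0.99 | 1.67 | 0.91 |
| 0.2 | 1.05 | 0.56 | 0.96 | 1.88 | 1.09 |
| 0.3 | 1.20 | 0.56 | 0.91 | 2.14 | 1.32 |
| 0.5 | 1.50 | 0.50 | 0.75 | 3.00 | 2.00 |

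The 2-df group-by-time test has noncentrality (46/2)d² / [1.5(1 − r)]. Taking d = 0.61 as an illustration for the scales, its power is 72% at r = 0.3, 86% at 0.5 and 98% at 0.7. The adjusted mean of T1 and T2 has 97%, 98% and 99.8%. The adjusted T2 comparison has 86%, 92% and 98%.

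**The case against.** The strongest reply is that nothing is wrong with the t test. Under randomization it is unbiased, and the planned completers exceed the stated power. That stands. A reader might infer that the principal analysis is invalid or underpowered, and the article's figures do not support that.

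The gain may also be slight. Baseline is taken in hospital around surgery, and intake is capped at entry, so r could be low. At r = 0.1 to 0.2 the gain is 0.4 to 1.5 percentage points. This also stands, and no large loss can be claimed for fluid intake without knowing r.

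On the scales, a reader might infer that the article says T0 is an outcome level, or that the group main effect is the test. It says neither. Both are inferred from the three time points and the reason given for the ANOVA, and that reason fits the group-by-time term at least as well. That term loses less at higher r. A reader might also apply the 2.1 to 3.0 multiplier to a T2 comparison. It belongs only to the mean of T1 and T2. Against an adjusted T2 comparison the multiplier is 1.3 to 2.0, and at r = 0.1 the main effect is slightly the more efficient.

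Stratified randomization answers the concern about imbalance only in part. The article does not say that baseline intake is a stratum, and adjustment gains precision even when the arms are balanced.

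Finally, changing a named principal analysis late in an open-label trial is not neutral. The abstract puts the end of data collection in September 2025 and analysis in December 2025. The Results section has T2 ending in October 2025. An interim efficacy and futility look after 74 participants was also planned. This objection stands and shapes the fix.

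**Conclusion.** The point holds as lost efficiency, not as an error of validity. For fluid intake, ignoring T0 costs about 0.4 to 12.6 percentage points of power over r = 0.1 to 0.6 (82.9% − 82.5% to 95.1% − 82.5%), probably towards the lower part of that range if the cap and the hospital baseline weaken the correlation.

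For WISQOL, PHQ-9 and eHEALS the loss can be larger. It rests on compound symmetry, equal effects at T1 and T2, and the inferred reading of the ANOVA, and its size depends on which term is tested. The case concerns fluid intake and these scales only. Recurrence, defined over the follow-up, has no baseline value to adjust for.

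The change is worth making because the baseline data are already in hand, but the trial's conclusions would not be unsound without it.

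**What to change.** Analyse fluid intake by ANCOVA, or a mixed model, with T0 intake as covariate at a named primary time point. Report the adjusted mean difference with its 95% CI, and keep the two-tailed t test as a sensitivity analysis. A t test of change from baseline is no substitute: at r = 0.3 its power is 69%, below the plain t test.

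For WISQOL, PHQ-9 and eHEALS, enter T0 as a covariate, keep only T1 and T2 as repeated outcomes, and name the contrast: the mean of T1 and T2, or T2.

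State, with a date, whether the change was made before anyone saw outcomes by arm, including at the interim look. If they had been seen, keep the t test as the planned principal analysis and report the baseline-adjusted estimate beside it, labelled as added later.

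The cost is one degree of freedom and a dated change of wording. No new data are needed.

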### Access to Data

The researcher is granted access to the complete trial dataset, with a contractual agreement established with the statistician to manage the data confidentially in accordance with the research protocol.

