## Results

This research has achieved notable advancements in assessing the efficacy of a nurse-led digital health intervention, WAFIR. The development of WAFIR, conducted in collaboration with a software developer, was finalized in February 2025, establishing a technological platform for the study. Recruitment, a critical initial stage, was fully completed, with all 148 participants enrolled from a tertiary hospital in Mainland China between March 1, 2025, and June 27, 2025, exclusively during the predischarge hospitalization period. Baseline data collection (T0) was completed by June 30, 2025, providing a solid baseline for longitudinal analysis. Follow-up assessments at the 1-month mark (T1) were finalized on July 31, 2025, while the 3-month follow-up (T2) is set to conclude in October 2025, aligning with the present date. Subsequent data analysis is scheduled for completion by December 2025, with dissemination of results planned through academic conferences and peer-reviewed publications throughout 2026.

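### The efficacy look has P<.05 as its only printed threshold, which gives about 7-8% false positives over two looks, and its 50% label compares completers with recruits

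*Protocol article*

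**What the plan says.** All the text is in the protocol article. Methods of Analysis plans a single interim analysis "to evaluate both efficacy (whether the intervention shows sufficient benefit to potentially stop the trial early) and futility". It is triggered "after 50% (74/148) of the target sample size have completed the primary end-point assessment". The primary analysis "will compare the fluid intake volume between the intervention and control groups using the 2-tailed *t* test". The same section then gives one criterion: "A significance level of *P*<.05 will be used to determine statistical significance". It states no separate interim threshold, no division of alpha between the looks and no method for judging futility.

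Sample Size computes the trial "with an α of .05, a power of 0.80, and an allocation ratio of 1:1", arrives at 92 participants, and adds: "Accounting for an attrition rate of 38%, as observed in this research, a total of 148 participants are anticipated to be recruited". So 92 is the number needed for analysis and 148 is the number to recruit.

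Results reports that all 148 were enrolled by June 27, 2025 and that T1 was finalized on July 31, 2025, while "the 3-month follow-up (T2) is set to conclude in October 2025". It does not mention whether the interim analysis was done.

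**The concern.** There are two separate problems.

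1. An efficacy look gives the trial a second chance to declare success. If both tests use P<.05, the overall false-positive rate exceeds the 5% assumed in Sample Size, and an ineffective applet would be declared effective more often than the stated level implies.

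2. The numerator of 74/148 counts people with primary data. The denominator counts people recruited, more than a third of whom the plan expects to lose. As a measure of how much of the final evidence is in hand, 50% disagrees with Sample Size. Spending boundaries and futility projections both need that measure, so a boundary derived for 50% would not suit a look at 80%.

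Because the article does not say whether the look happened, a reader cannot tell which final significance level applies.

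**Working it through.** **Inputs.** From Sample Size: 92 evaluable, 38% attrition, 148 recruited, α .05. From Methods of Analysis: 74 completers at the look, two-tailed t test, P<.05.

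**The plan's own figures.**
- Recruitment: 92 / (1 − 0.38) = 148.4, which matches 148.
- Label: 74 / 148 = 0.50, correct as a fraction of recruits.

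**Information at the look.**
- Expected completers: 148 × 0.62 = 91.8, about 92.
- Fraction: 74 / 92 = 0.804.
- Participants who must have reached the assessment time to yield 74 completers: 74 / 0.62 = 119.

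**Type I error with P<.05 at both looks.** Under no effect, the interim and final statistics Z1 and Z2 are approximately bivariate normal with correlation √t, where t is the information fraction. The overall error is P(|Z1| > 1.96 or |Z2| > 1.96), with no futility stop.

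| Attrition | Completers | t | Overall error |
|---|---|---|---|
| 38% | 92 | 0.80 | 7.1% |
| 30% | 103.6 | 0.71 | 7.5% |
| 20% | 118.4 | 0.63 | 7.9% |
| 10% | 133.2 | 0.56 | 8.1% |
| 0% | 148 | 0.50 | 8.3% |

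Simulation of 200,000 trials with actual t tests gave 7.1% for a final 92 and 8.3% for a final 148.

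**Thresholds that hold about 5% overall.**
- Interim .001, final .05: overall 0.0500 at t = 0.804 and 0.0502 at t = 0.5.
- O'Brien-Fleming-type spending: .025 then .043 at t = 0.804; .003 then .049 at t = 0.5.
- Pocock-type at t = 0.804: .035 at both looks.

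If P<.05 was itself the interim rule, the look alone uses 5%. Any final test then adds P(no rejection at the look, rejection at the end), so no final level above zero brings the total back to 5%.

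**Futility, conditional on the denominator used.** Conditional power under the current trend is Φ[(z1√t + θ(1 − t) − 1.96) / √(1 − t)], with θ = z1/√t.

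| Interim z1 | Final 92 (18 to come) | Final 148 (74 to come) |
|---|---|---|
| 1.00 | 3% | 22% |
| 1.25 | 10% | 39% |
| 1.50 | 26% | 59% |

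For z1 = 1.00 and t = 0.804: z1√t = 0.897 and θ(1 − t) = 1.115 × 0.196 = 0.218, so (0.897 + 0.218 − 1.96) / 0.442 = −1.91, and Φ = 0.03.

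**Sensitivity to the 92.** A two-tailed t test at the stated d of 0.61 needs 88. With 88 expected completers t = 74/88 = 0.84 and the error is 6.9%, so the conclusion is unchanged.

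**The case against.** The strongest reply is that the article never says P<.05 is the interim stopping rule. That sentence is a general one, and boundaries are often left to an analysis plan, which is not shown here. This stands as a limit: the 7-8% describes the printed rule if it is followed at both looks, and a stricter boundary may exist elsewhere. It does not remove the point, because the article plans an efficacy stop, prints one unadjusted level and refers to no other.

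It is also fair that 74/148 is correct arithmetic, that the text calls it a share of the target sample size and not an information fraction, and that 38% is a planning allowance. With 0-20% attrition the fraction would be 50-63%. The label is not what causes the inflation: correcting it moves the error from 8.3% down to 7.1%.

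Four stronger readings are tempting and are not supported:

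- **Futility will be judged against 148.** No futility calculation is given. This would be an inference from the label, so the conditional-power figures show only what would follow if 148 were used.
- **A final P between .043 and .05 is not significant.** That holds for O'Brien-Fleming-type spending at 80%. With an interim threshold of .001 the final test stays at .05.
- **The look should move to 46 completers for a true 50%.** With enrolment complete and T1 closed, that is probably no longer possible.
- **The Access to Data section exposes interim results by arm.** Its statement that "The researcher is granted access to the complete trial dataset" concerns the full dataset and its confidential handling, and says nothing about interim results.

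Finally, no early stop is reported and all 148 were enrolled, so harm from stopping early appears not to have arisen. The final significance level remains open.

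**Conclusion.** The concern holds in this form. An efficacy look with P<.05 as the only printed level gives an overall two-sided error of about 7-8% (7.1% at 80% information, 8.3% at 50%), not the .05 used in Sample Size. This rests on applying P<.05 at both looks, on the normal approximation (confirmed by simulation), and on no futility stop; a binding one would lower the error somewhat. It does not depend on actual attrition between 0% and 38%.

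Secondly, on the plan's own attrition the look falls at about 80% of the expected primary data. Spending boundaries and futility projections should be based on expected completers. Harm to the futility decision is conditional, since its method is not stated.

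The point bears on the validity of the primary claim and should be settled before the final result is interpreted.

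**What to change.** In Methods of Analysis, state whether the interim look took place. The dates in Results suggest that its trigger has probably passed.

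- **If it did not take place:** delete it and keep the final test at .05.
- **If it did:** report it with the efficacy threshold that was fixed beforehand.
  - If that threshold was P<.001, the final test can stay at .05 (overall error about 5.0%).
  - If it was an O'Brien-Fleming-type spending boundary, use the final level that matches the actual information fraction (about .043 at 80%).
  - If no stricter threshold was fixed beforehand, so that P<.05 applied at the look, use a final level that accounts for the look and do not describe the result as controlled at 5%. A boundary chosen afterwards does not restore that control.

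Describe the look as 74 of about 92 expected completers (about 80%), base any futility projection on expected completers, and treat futility as non-binding.

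The cost is a few sentences, with no more participants. With P<.001 at the look, power at d = 0.61 and 46 per arm is essentially unchanged at about 83%. With O'Brien-Fleming-type spending at 80% it is 82.6% against 83.3% for a single test (normal approximation).
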